### **3.13 Monitoring**

#### **Data Monitoring and Safety (DSMC) and interim analysis:**

A DSMC does not seem necessary as there are no anticipated risks from participating. All wait-listed patients will be receiving standard of care, and there are no anticipated adverse events expected from a care coordination intervention. However, to detect early superiority, futility, or inferiority of the intervention, interim analyses are planned using the outcome data collected at 6 and 12 months. The trial PI and Steering group will be informed if a pre-defined change in the frequency of key patient and family outcomes is observed, whether positive or negative.

**Adverse Event Reporting:** While there are no adverse events expected in the context of the intervention being administered, any adverse events will be reported to the Research Ethics Board. All adverse events and adverse reactions will also be reported to the PI within 24 hours.

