### 3.6 Sample Size

For the RCT, we conservatively project the total sample size to be 140 (70/arm) based on the following criteria: i) Two-sided test of the null hypothesis at the 5% level; ii) Power of 80%; iii) 10% lost-to-follow-up; projected smallest clinically important difference of 0.5 of the within-patient standard deviation, which is recommended by the developer as a moderate effect size (39).

The required sample size is considered feasible as it is estimated that a pool of about 250 patients are readily identifiable for recruitment at CCKO sites.

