These scores will be used as three co-primary outcomes. The appropriate descriptive statistics will be used to compare groups with respect to baseline and demographic variables. Each outcome variable at Month 12 will be compared between groups using an ordinal regression incorporating center as a random intercept and adjusting for the baseline score. A two-sided test of hypothesis will be applied. The Holm-Bonferroni method will be used to deal with multiple testing (the three outcomes), where the overall target type I error rate is 0.05. The principle of intention-to-treat will be applied to the final analysis.

- iv) Child and Parent (Secondary) Outcomes: The data collection at 0 months and 6 months will be used to perform test-retest reliability, to establish baseline reference measures (0, 6, 12 months for this and other phases of intervention), and to assess for stability of outcome changes (24 months). Secondary child and parent outcomes will be compared at 0, 6 and 12 months using Bonferroni corrections to account for multiple testing. All secondary health system outcomes will be compared between the intervention and control as well.

- v) Process Outcomes: Process data collected through patient interviews will be first analyzed one participant at a time without making distinctions regarding the specific sample criteria articulated above. Following that, distinct issues brought forward for the specific sample criteria will be compared and contrasted to the main sample results. All interview data will be analyzed using a descriptive approach. The overarching themes will be selectively coded using the categories of ‘Active Ingredients’, ‘Fidelity’, ‘Dose’, and ‘Context’. The specific sub-themes under these pre-selected themes will be coded inductively.

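### Interim looks for early superiority sit outside the stated 0.05, so overall type I error control is not assured as the protocol is written

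*Protocol*

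**What the plan says.** **Interim looks.** Protocol section 3.13 considers a monitoring committee unnecessary, then adds that "to detect early superiority, futility, or inferiority of the intervention, interim analyses are planned using the outcome data collected at 6 and 12 months". The only consequence it attaches is this: "The trial PI and Steering group will be informed if a pre-defined change in the frequency of key patient and family outcomes is observed", in either direction. It gives no interim significance level, boundary or stopping rule.

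**Final analysis.** Section 3.12 states: "These scores will be used as three co-primary outcomes". It continues: "Each outcome variable at Month 12 will be compared between groups using an ordinal regression", adjusted for the baseline score, and "A two-sided test of hypothesis will be applied". On multiplicity it says: "The Holm-Bonferroni method will be used to deal with multiple testing (the three outcomes), where the overall target type I error rate is 0.05". The correction therefore covers the number of outcomes and does not mention the number of looks.

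**Sample size.** Section 3.6 lists "Two-sided test of the null hypothesis at the 5% level", 80% power, 10% loss and a "projected smallest clinically important difference of 0.5 of the within-patient standard deviation", giving 140 in total. It makes no reference to interim testing.

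**Setting.** Under section 3.9, patients and investigators are not blinded, while data analysts are blinded to enrolment period. The primary outcomes are parent-reported survey scores (sections 3.4 and 3.12).

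**The concern.** Detecting early superiority is an efficacy purpose, not only safety monitoring. A trial that may claim success at 6 months and again at Month 12 has two chances of a false positive on each outcome. The overall 0.05 in section 3.12 is already fully used by the Month 12 tests, so an early claim at any level would come on top of it.

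Two features of the same paragraph add to the difficulty. First, it lists 12 months as an interim look, although Month 12 is the primary comparison, and does not say how the two analyses differ. Second, it routes observed changes, good or bad, to the PI and Steering group of an unblinded trial with parent-reported outcomes. Each family's 6-month data come before its Month 12 questionnaire. A between-arm result could therefore reach the study team while primary data are still being collected. That second concern does not depend on whether anyone makes an early claim.

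**Working it through.** **1. Reproduce the sample size.** Inputs from section 3.6: two-sided alpha 0.05, power 80%, difference 0.5 SD, loss 10%. The 1:1 allocation is from section 3.8.

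- n per arm = 2(1.960 + 0.842)² / 0.5² = 62.8, rounded up to 63; power at 63 per arm is 0.801.
- Allowing for loss: 63 / 0.90 = 70 per arm, 140 in total.

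The stated 140 reproduces exactly from one test at the full 5%. It contains no allowance for another look.

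**2. One outcome, unadjusted 0.05 at both looks.** Let Z6 and Z12 be the test statistics at 6 and 12 months, bivariate normal with correlation ρ and no effect at either time. Then

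error = 1 − P(|Z6| ≤ 1.96 and |Z12| ≤ 1.96).

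The protocol gives no value for ρ, so a range is shown. At ρ = 0 the result is 1 − 0.95² = 0.0975.

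**3. Three outcomes.** At each look the smallest p-value is compared with 0.05/3 = 0.0167, the first Holm step, which governs the family-wise error when all nulls are true. This used 1,000,000 simulated trials per setting. The inter-outcome correlation is also assumed.

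| Either look significant | ρ = 0.3 | ρ = 0.5 | ρ = 0.7 | ρ = 0.9 | Month 12 only |
|---|---|---|---|---|---|
| One outcome | 0.0951 | 0.0907 | 0.0835 | 0.0704 | 0.05 |
| Three outcomes, inter-outcome correlation 0 | 0.0940 | 0.0911 | 0.0845 | 0.0714 | 0.049 |
| Three outcomes, 0.3 | 0.0916 | 0.0883 | 0.0816 | 0.0690 | 0.047-0.048 |
| Three outcomes, 0.5 | 0.0858 | 0.0816 | 0.0761 | 0.0643 | 0.044-0.045 |

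The ranges are 7.0-9.5% for one outcome and 6.4-9.4% family-wise. Month 12 alone stays within 5%.

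**4. What the 12-month interim look could mean.** If it uses the complete Month 12 data, it is the primary test and adds nothing to step 2. If it means a look at part of the Month 12 data before the rest arrive, it is a third look. With half the data assumed available, and all three looks unadjusted, the one-outcome error is 0.114-0.126 for ρ from 0.7 down to 0.3. The text does not say which is meant.

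**5. Check the remedy.** With p<0.001 required at 6 months and Month 12 left at 0.05, the one-outcome total is 0.0508, 0.0506, 0.0502 and 0.0500 for ρ = 0.3, 0.5, 0.7 and 0.9. For three outcomes a simple upper bound is 0.05 + 3 × 0.001 = 0.053.

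**6. No efficacy claim at an interim look.** Only the Month 12 family can then produce a claim, and the error is that of the last column.

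**The case against.** The strongest reply is that section 3.13 never says an interim look can stop the trial or support a superiority claim, nor at what level it would be tested. The stated consequence is notification. On that reading the Month 12 Holm procedure is the only confirmatory test and nothing is inflated. The reference to a pre-defined change suggests a threshold exists somewhere, and a statistical analysis plan that is not at hand may set it. This part stands. A reader might infer that the 5% error rate is definitely breached, or that 9% is the plan's actual error rate, but the text does not support either. The figures above hold only if early claims are allowed at an unadjusted level.

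It can also be said that a 12-month analysis is interim to a study that collects data to 24 months and repeats its analyses for Year 2 (sections 3.3, 3.4 and 3.12). That is a possible meaning. But the sentence ties the look to early detection of superiority at the time point where the primary test is made, so it still needs clarifying.

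On information flow, a reader might infer that by-arm results will be handed to the PI, or that the PI's team delivers the intervention. Neither is stated. Section 3.13 does not say what is shared or in what form. Section 3.3 places fidelity oversight with the provincial council, and section 4.3 says only that the PI and co-PI helped to craft the strategy. Analysts are blinded to enrolment period, and families know their own arm in any case. An effect on their answers is therefore a risk, not a demonstrated bias.

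What the reply does not remove is that the protocol names early superiority as a purpose while section 3.12 confines its overall 0.05 to three outcomes at Month 12. Any early-claim boundary set elsewhere would still have to be reconciled with that sentence.

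**Conclusion.** The point holds as a lack of assurance, not as a demonstrated breach. The protocol plans looks for early superiority and commits all of its overall 0.05 to Month 12. It does not say whether an early look can yield a claim.

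The possible cost runs from none, if the looks carry no efficacy claim, to the 7.0-9.5% (one outcome) and 6.4-9.4% (family-wise) worked out above, if superiority may be claimed unadjusted at 6 months or Month 12. The correlations and the interim test level are assumptions. Inflation was present at every correlation tried, so the conclusion does not hinge on one value. Labelling the primary time point as interim, and reporting observed changes to the study leadership of an unblinded trial, are separate ambiguities in the same paragraph that should be settled with it.

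**What to change.** Change section 3.13 as follows.

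1. Remove 12 months from the interim sentence, so that Month 12 is only the primary analysis.
2. Preferably, delete early superiority and state that the Month 12 Holm procedure is the only efficacy test. If an early claim must stay, require p<0.001 per outcome at 6 months (Haybittle-Peto) and say so in section 3.12 as well. The one-outcome total is then about 5.0-5.1%. If strict family-wise control is wanted, running the Month 12 Holm procedure at 0.05 − 0.003 = 0.047 guarantees it.
3. State that 6-month between-arm results are not released to the PI or Steering group before Month 12 data collection is complete, except where the pre-defined harm or futility threshold is crossed.

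Section 3.12 already refers to an original analysis. If looks have been taken, the report should say whether a 6-month comparison was made and what was decided from it.

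The cost is a few sentences and no extra patients. The downside is giving up an early success claim that the present error control does not protect.

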## **4.0 Ethics and Dissemination**

### **4.1 Research Ethics Approval**

The protocol will be reviewed by Research Ethics Boards at all participating sites. Study participants will be asked to provide written informed consent which will be obtained by the study Research Coordinator at SickKids and Research Assistants at other sites. The study Research Coordinator or Research Assistant will obtain informed consent from parental caregivers. Informed consent/assent will be obtained from all those who are able to provide it. Patients who decline to participate in the collection of PROMs and PREMs will be offered to consent for use of data on health services use from readily available administrative data. Health service data will also be collected on those who are excluded from participating (e.g. due to linguistic barriers or over 16 years old) by waiver of consent.

### **4.2 Confidentiality**

All study data will be kept confidential by removing personal identifying information, and all study files will be maintained on a secure server with password protection. Anonymity will be maintained for research participants through the presentation of aggregate data in all presentations and publications.

### **4.3 Dissemination policy**

Knowledge translation (KT) activities will be facilitated by the leadership of team investigators locally, nationally and internationally. CCKO represents a fully integrated KTE paradigm. The PI and co-PI have worked with patients and PCMCH to craft the provincial strategy, providing population-based ICES data to understand the target population (numbers/location of children, patterns of care, health system costs), and clinical expertise in complex care. The committees overseeing implementation and evaluation encompass key knowledge users (patients, families, clinicians, administrators), allowing for seamless KT. PCMCH is providing some evaluation support for this project and will be accountable to MOHLTC for the evaluation. Executive Summaries and/or Presentations will be shared for wide dissemination to a variety of organizations/collaboratives including provincial associations (e.g. OACRS, OACCAC, OHA) and the Canadian Association of Pediatric Health Centres Complex Care Community of Practice. Academic KT will occur through presentation at major health policy forums (e.g. CAHSPR) and publications in high-impact, peer-reviewed journals.

At the end of the study, a study summary will be shared on PCMCH's online portal, which describes the key findings of the intervention. A basic demographic overview would be provided (to give a sense of the study sample), as well as key findings related to service delivery outcomes and families' overall experience with the key workers and care plans.

Appendix 1 – Strategic Framework for CCKO

[figure not shown]

# Appendix 2 – CCKO Planning and Implementation Regions

| Region | LHINs Included                                                                                           | Primary Tertiary Hospital
Serving Target Population | Children with persistent high
health service utilization |                          |
|--------|----------------------------------------------------------------------------------------------------------|--------------------------------------------------------|-------------------------------------------------------------|--------------------------|
|        |                                                                                                          |                                                        | Estimated
# in Region                                    | % of total
population |
| 1      | Erie St. Clair & South West                                                                              | London Health Sciences                                 | 885                                                         | 14.1%                    |
| 2      | Hamilton Niagara Haldimand Brant
& Waterloo Wellington                                                | Hamilton Health Sciences                               | 1118                                                        | 17.8%                    |
| 3      | Toronto Central, Mississauga
Halton, Central West, Central,
Central East & North Simcoe
Muskoka | Hospital for Sick Children                             | 3064                                                        | 48.6%                    |
| 4      | Champlain & South East                                                                                   | Children's Hospital of Eastern
Ontario              | 823                                                         | 13.1%                    |
| 5      | North East & North West                                                                                  | Mixed                                                  | 400                                                         | 6.4%                     |

[figure not shown]

London Health  
Sciences Centre

[figure not shown]

Hamilton  
Health  
Sciences

SickKids

[figure not shown]

Supplement: Supplement 1. — Trial protocol [file jamapediatr-e230115-s001.pdf]
